### **4. Measures to determine the preliminary cost-effectiveness of BSMART**

Cost components and incremental costs. The cost-effectiveness of interventions will be compared based on the 7-day point prevalence abstinence at 6 months. The analysis will adopt a healthcare system perspective and calculate direct medical costs associated with the implementation of each strategy. Fixed costs include any set-up costs associated with the implementation of the interventions (e.g., supplies, information technology infrastructure, baseline staff training) and will be collected at week 0. Variable costs include ongoing staff or lay case manager and nurse contact time with study participants, and follow-up training (time and material costs). Variable costs will be collected at week 12 and quarterly thereafter. Time will be valued using prevailing wages that are applicable to the staff expertise. The calculation of the 6-month costs for the control and implementation phases will involve summing across each of the cost

components at the individual level to provide an estimate of the period cost (per individual and average period cost for each of the strategies. The incremental cost of the interventions will be defined as the difference in average costs when comparing the implementation period to control period. The incremental cost of implementing BSMART = ((‘component A’ cost per person x number of persons for implementation period) + (‘component B’ cost per person x number of persons for implementation period) +...) – ((‘component A’ cost per person x number of persons for control period) + (‘component B’ cost per person x number of persons for control period+ ...)). The quarterly cost calculation accounts for the censoring of data due to loss to follow-up or administrative censoring using an inverse probability-weighting  approach.

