### Statistical analysis for study Objective 4.

Incremental cost-effectiveness ratio and net monetary benefit. The incremental cost-effectiveness ratio (ICER) is calculated as the ratio of the difference in mean costs and the difference in mean 7-day point prevalence abstinence at 6 months. The ICER (Figure 6) quantifies the additional cost associated with a

$$\text{ICER} = \frac{\text{Cost}_{\text{Implementation}} - \text{Cost}_{\text{Control}}}{\text{Effect}_{\text{Implementation}} - \text{Effect}_{\text{Control}}}$$

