**Fig 6: ICER**

unit change in the 7-day point prevalence abstinence at 6 months, comparing between the implementation and control groups. Net benefit (NB) regression provides an appropriate approach to quantify the ICER using the incremental net monetary benefit (INMB) and produce a confidence interval around the ICER.

In equation 1 of Figure 7 we define NB as the difference between the monetized total effect measure (the product of lambda, the willingness to pay per unit of effect, and the total effect units available, e) and the associated costs. The NB regression model is specified in equation 2 of Figure 7 as the difference between effects and costs, estimated via a parametric regression framework where errors are represented by the final term in equation 2, epsilon. Alternative formulations of equation 2 include a generalized linear regression model that incorporates a skewed distribution of the NB. We will identify the initial value of lambda following a targeted literature review and consultations with onsite study collaborators. In equation 2 of Figure 5, the NMB, represented by the  $\beta$  coefficient on the indicator variable for receipt of intervention (i.e., 'Implementation'), will be estimated using the NB regression model.

$$NB_{ij} = (\lambda - e_{ij}) - c_{ij} \dots \dots \dots (1)$$

$$NB_{ij} = \beta_0 + \beta_1 \times \text{implementation}_{ij} + \epsilon_{ij} \dots \dots \dots (2)$$

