|                           | Hourly wage                                                                                      |
| Cost of varenicline use   | Varenicline dose (for 12 weeks)                                                                  |
|                           | Staff time for participant assessment for eligibility for varenicline use                        |
|                           | Patient transportation for drug pick ups                                                         |
|                           | Cost of managing adverse events                                                                  |
|                           | Staff time for adverse event management                                                          |
| Cost of follow-up visits  | Participant transport weekly for the first four weeks and monthly for two months then at week 24 |
|                           | Staff costs for follow-up visits                                                                 |

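### Objective 4: the displayed incremental-cost expression contradicts the plan's own mean-cost definitions, and the net-benefit regression has no calendar-period or facility term

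*Protocol*

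**What the plan says.** In the Protocol, Measures to determine the preliminary cost-effectiveness of BSMART, costs are summed for each individual to give a period cost, "per individual and average period cost for each of the strategies". The section then states: "The incremental cost of the interventions will be defined as the difference in average costs when comparing the implementation period to control period". The expression that follows is a sum over components of "cost per person x number of persons for implementation period", minus the same sum for the control period.

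In Statistical analysis for study Objective 4, the ICER is "calculated as the ratio of the difference in mean costs and the difference in mean 7-day point prevalence abstinence at 6 months". Net-benefit regression is to give the INMB and a confidence interval around the ICER. Equation 2 (Fig 7) has an intercept, an implementation indicator and an error, "estimated via a parametric regression framework where errors are represented by the final term in equation 2, epsilon". The only alternative named is a generalized linear model for skewed net benefit.

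Elsewhere, Study Design gives control for the effect of time as a reason for choosing the stepped wedge. The Objective 1 model has random effects for clustering within facilities and periods and a fixed effect for facility type. Nothing carries these terms over to Objective 4.

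The cost section adopts a healthcare-system perspective with direct medical costs. Appendix H lists "Patient transportation for drug pick ups" and participant transport to follow-up visits. It lists CO monitoring under the cost of BSMART but not under the cost of SOC.

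**The concern.** The displayed expression is the only explicit formula for incremental cost, so an analyst could follow it instead of the sentence before it. Differences in recruitment between the phases would then appear as cost.

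The INMB is the stated estimand of Objective 4, and the results are meant to inform the ministry and the national agency. Net benefit contains the primary endpoint, so it is exposed to the same time trend and clustering that the primary model has to handle. Background change in smoking is plausible here: the Background section reports a Tobacco Control Bill passed and awaiting signature. Without a calendar-period term, beta_1 in equation 2 cannot separate such a change from the effect of BSMART.

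A lesser matter is that cost items outside the stated perspective, or incurred in both phases but listed in one, would raise incremental cost if they entered the base case.

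**Working it through.** **Inputs.** From the protocol: 15 facilities, 25 participants per cluster-period, 375 per phase, control abstinence 10%, effect +10 points, loss 5%, ICC 0.02. Assumed because not given: two-sided alpha 0.05, per-person costs, the stability of facility effects across periods (autocorrelation 1, 0.5 and 0), and the size of any trend.

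**The plan's own figure.** Objective 4 states no number, so the inputs are checked on the power statement. Cluster-period size after loss is 25 × 0.95 = 23.75. The design effect is 1 + (23.75 − 1) × 0.02 = 1.455, and the effective n per condition is 15 × 23.75 / 1.455 = 244.8. Power for 10% against 20% is 0.875 (pooled variance), which agrees with the stated 87%.

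**Incremental cost.** Take assumed mean costs of 10 (control) and 200 (implementation). The difference in means is 190 whatever the enrolment. The displayed expression gives:

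| Control / implementation | Expression | Result |
|---|---|---|
| 375 / 375 | 200 × 375 − 10 × 375 | 71,250 |
| 350 / 400 | 200 × 400 − 10 × 350 | 76,500 |
| 400 / 350 | 200 × 350 − 10 × 400 | 66,000 |

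With equal costs of 100 per person at 350 / 400, the expression gives 40,000 − 35,000 = 5,000, although the mean difference is 0.

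The ICER from means is 190 / 0.10 = 1,900 per extra quitter at every split. Totals over total quitters also give 1,900 at 375 / 375. They give 76,500 / (80 − 35) = 1,700 at 350 / 400 and 66,000 / (70 − 40) = 2,200 at 400 / 350.

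**Secular change.** In Table 1, implementation falls one year after control in all three steps. Without a period term, E(beta_1) = true effect + one year of secular change. In simulation of equation 2 (3,000 runs per setting, Table 1 layout, 25 per cluster-period, ICC 0.02 to 0.10), a trend of 0.1 SD per year biased beta_1 by 0.1 SD. Coverage of the nominal 95% interval fell to about 66–73%. For abstinence, 0.1 SD is 0.1 × √0.125 ≈ 3.5 points.

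**Standard error of the abstinence part.** The average binomial variance is (0.09 + 0.16)/2 = 0.125, with 15 × 23.75 = 356.25 per phase.

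- Reported under independent errors: √(0.25 / 356.25) = 0.0265.
- True SE of the same contrast: √{(2/15) × [0.125 × 0.98 / 23.75 + 0.125 × 0.02 × (1 − r)]}, where r is the autocorrelation of the facility effect.
- Period-adjusted SE: generalised least squares with four calendar-year effects and the same covariance.

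| r | True SE, equation 2 | Reported / true | Period-adjusted SE |
|---|---|---|---|
| 1 | 0.0262 | 1.01 | 0.0358 |
| 0.5 | 0.0292 | 0.91 | 0.0375 |
| 0 | 0.0320 | 0.83 | 0.0391 |

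Simulated coverage without trend at ICC 0.02 was about 95%, 92% and 89% in the same order. At ICC 0.10 and r = 0.5 it was 81%.

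**Cost inputs.** Tables 2 and 3 schedule breath CO at baseline, week 12 and week 24 in both phases. Appendix H has a CO line in the BSMART cost table only; the SOC table has staff time and the brochure.

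**The case against.** The strongest reply on cost is that the protocol does not adopt totals. The sentence before the expression and the Objective 4 definition of the ICER both say means, and nothing feeds the expression into the ICER. This stands. A reader might infer that the ICER would come out too large by a factor of the number of persons per phase, but that requires totals over a difference in proportions, a combination the protocol never states.

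On precision, a reader might set 0.0265 against 0.0358 and conclude that the interval is about a quarter too narrow. That does not follow, because the two figures belong to different estimators. Period terms alone, at ICC 0, already raise the SE from 0.0265 to 0.0324. With stable facility effects each facility contributes equally to both phases, and the simple interval covers at about 95% when there is no trend.

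It can also be said that equation 2 is open to other forms, that its cited method allows covariate adjustment, that an SAP may specify more, and that the objective is labelled preliminary. These points moderate the weight but do not answer the concern. The only alternative named deals with skewness, and the displayed model is the one tied to the INMB and the ICER interval.

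Equation 1 as it reads here shows a minus sign where the text says product. That may be a misread multiplication sign in the PDF, so no weight is placed on it.

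Appendix H is a collection form and does not fix the base case. This stands, so its mismatch with the perspective is secondary.

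**Conclusion.** Two points hold. First, the displayed incremental-cost expression contradicts the mean-difference definitions given beside it and in the ICER definition. The harm arises only if the expression is used, and then the result depends on enrolment.

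Second, equation 2 omits calendar period and facility. The missing period term is the more serious omission: any one-year secular change enters beta_1 one for one, and its size is unknown. The missing facility structure matters only if facility effects vary between periods. The reported SE for the abstinence part is then about 9% too small at autocorrelation 0.5 and about 17% too small at 0, given ICC 0.02. These figures cover the effect component only, since the protocol gives no variance or ICC for costs.

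A reader might go further and call the ICER and INMB interval invalid. The documents do not support that: the ICER is defined on means, and without trend and with stable facility effects the interval is sound. The conclusion is that the INMB is not protected against trend or cluster-period variation. The transport and CO items are consistency points whose effect on cost cannot be sized from the protocol.

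**What to change.** 1. Divide each bracket of the incremental-cost expression by the number of persons in that phase, so that it matches the mean-cost definitions.
2. Extend equation 2 with fixed effects for calendar period and facility type and random effects for facility and facility-period. Alternatively, bootstrap the period-adjusted model by resampling facilities.
3. State that patient and participant transport stays out of the base case under the healthcare-system perspective, and treat CO monitoring the same way in both phases.

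This is rewording of one formula, one model and one appendix, with no new data. The cost is a wider INMB interval: for the abstinence part the SE rises from 0.0265 to about 0.036 to 0.039, which is the price of removing the trend from the estimate.

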### Estimating process and outcome measures

All procedures will be conducted according to the local standards of routine clinical care. The following measures will be utilized:

1. **Baseline Demographic Information:** Baseline information will be abstracted from the HIV medical records and collected using a questionnaire. Baseline information will include demographics, medical history, laboratory values measured as part of HIV care (e.g. viral load, CD4), antiretroviral (ARV) history and ART treatment regimen (for current patients), and ART treatment start date. Because of high viral load suppression and high retention rate in this population, we will not be analyzing HIV treatment variables as mediators or outcomes.
2. **5”A”s (SBIRT) checklist:** This checklist will be completed by the LHW case managers and will serve to document the delivery of the intervention. A 10% random sample of the completed 5”A”s checklist will be reviewed by [name] during the time that a site is engaged in the intervention to ensure fidelity to the study intervention.
3. **Intake Smoking History Questionnaire** will measure length of smoking, use of other tobacco products, quit attempts, length of longest quit attempt, and smokers in the immediate living environment.
4. **Follow-up Smoking Use Questionnaire** will measure 7-day and 30-day point prevalence abstinence, number of cigarettes smoked (if not abstinent), stage of change and readiness to quit (if not abstinent), length of longest period of abstinence since last evaluation, use of varenicline, side effects, reasons for using or not using varenicline, and length of varenicline use.

5. **Stages of Change Algorithm** and **the Readiness Ruler**, will be used at baseline and follow-up to determine each individual's stage of change for quitting tobacco.
6. **Smoking Abstinence**: Abstinence will be based on self-reported 7-day point prevalence abstinence confirmed by expired CO < 6 ppm. Abstinence criteria must be met in participant Month 6 or at an earlier study week and maintained through participant Month 6 to be considered a responder. We will use coVita CO Smokerlyzer, a single-breath point-of-care tool designed specifically for use in smoking cessation programs and clinics.

For those who agree to be treated with varenicline:

7. **Adherence to Medication**: Pill and counseling adherence will be assessed at Weeks 0, 1, 2, 4, 8, and 12. Pill adherence will be tracked by the following question at each medication visit: How many days in the last week did you take at least one of your study pills. Pill adherence will be defined by participant self-report of taking six or seven pills at week eight which coincides with their last receipt of varenicline.
8. **Adverse Event Monitoring** (Baseline, weekly for 4 weeks then every 4 weeks until week 12): Adverse events will be monitored at each study contact and classified and graded using the Common Terminology Criteria for Adverse Events and Common Toxicity Criteria provided by the National Cancer Institute. Our protocol for responding to Serious Adverse Events is summarized in the Human Subjects section.  
  
The 5 "A"s (SBIRT) Checklist and the Intake Smoking History Questionnaire will be administered at baseline for PLWH newly enrolling to HIV treatment and those currently on HIV treatment. A Follow-up Smoking Use Algorithm will be administered at baseline and at 4-, 12-, and 24-weeks of follow-up. The CO measurement will be obtained at baseline, 12 and 24 weeks of patient follow-up using coVita CO Smokerlyzer .

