As analysis of secondary outcomes at 6 months, 30-day point prevalence abstinence will be compared between the implementation and the control groups in a similar model to the one used in the analysis of the primary outcome. Longitudinal differences in the Stages of Change Algorithm between the implementation and the control groups will be compared using random-mixed effect regression. Analysis will be conducted to assess factors associated with completion of varenicline regimen using generalized estimating equation model for binary repeated measures.

## Statistical analysis for Study Objective 2

The CFIR will be used to guide qualitative interviews and activity log coding analysis. The CFIR-ERIC Matching Tool, which provides a menu of 39 constructs across five domains (Intervention Characteristics, Inner Setting, Outer Setting, Characteristics of Individuals, and Process), will be used to generate a list of potential strategies to address implementation barriers.

Qualitative data analysis. The CFIR will provide the structure for the initial codebook to guide qualitative data and activity log data using a descriptive content coding approach. The coding approach will be both deductive (codes derived from CFIR constructs) and inductive (codes derived from the data). During the coding and rating phases of analysis, the analysts will be blinded to the implementation effectiveness. Data will be independently coded by a revolving team of two analysts. Codes will be compared, and differences will be resolved by consensus discussion.

Quantification of qualitative data. We will quantify qualitative data and activity log data by having two analysts independently assign ratings for each code to reflect its positive or negative impact on implementation. Ratings will range from -2 to +2 with 0 to reflect a neutral or mixed influence of the code. For each facility, data will be consolidated, and two analysts will independently rate each code across all the interviews to obtain a facility rating for each time period. This process will be repeated for the two rounds of interviews and monthly for activity logs.

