### BSMART Medication Adherence Form

|                           |                        |
|---------------------------|------------------------|
| Researcher ID:     | Participant ID: |
| District:          | Facility:       |
| Date: (dd/mm/yyyy) |                        |

(Completed only at Week 1, 2, 3, 4, 8, and 12)

|                                 |                                 |                                 |                                 |                                 |                                  |
|---------------------------------|---------------------------------|---------------------------------|---------------------------------|---------------------------------|----------------------------------|
| Week:                    |                                 |                                 |                                 |                                 |                                  |
|  Week 1 |  Week 2 |  Week 3 |  Week 4 |  Week 8 |  Week 12 |

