**How many days last week did you take at least 1 of your study pills?**

\_\_\_\_\_

(Completed only at week 2, 3, 4, 8, and 12)

|                                 |                                 |                                 |                                 |                                  |
|---------------------------------|---------------------------------|---------------------------------|---------------------------------|----------------------------------|
| Week:                    |                                 |                                 |                                 |                                  |
|  Week 2 |  Week 3 |  Week 4 |  Week 8 |  Week 12 |

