**How many days last week did you take at least 2 of your study pills?**

\_\_\_\_\_

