### Protocol Prescription

Days 1-3: Dates \_\_\_\_\_

Varenicline (0.5mg, total 0.5mg daily): take one tablet (0.5mg) daily, one tablet in the morning after eating and with a full glass (8 ounces) of water.

Days 4 - 7: Dates \_\_\_\_\_

Varenicline (0.5mg, total 1mg daily): take one tablet (0.5mg) twice daily, one tablet in the morning and one tablet in the evening, after eating and with a full glass (8ounces) of water.

Weeks 2 - 12: Dates \_\_\_\_\_

Varenicline (0.5mg, total 2mg daily): take two tablets (1mg) twice daily, two tablets in the morning and two tablets in the evening, after eating and with a full glass (8ounces) of water.

Prescribers Name: \_\_\_\_\_

Prescribers Signature: \_\_\_\_\_

Date: \_\_\_\_\_

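### The adherence rule counts pills where its question counts days; read as days, it guarantees only 21–25% of week 8's prescribed tablets, ignores weeks 9–12, and comes with three conflicting assessment schedules

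*Protocol*

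**What the plan says.** Under *Estimating process and outcome measures*, item 7, the protocol tracks adherence at each medication visit with one question: "How many days in the last week did you take at least one of your study pills". It then sets the threshold: "Pill adherence will be defined by participant self-report of taking six or seven pills at week eight", a time point that it ties to the last supply of the drug.

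The Medication Adherence Form (Appendix C4) has two items, both answered in days. The first is "How many days last week did you take at least 1 of your study pills"; the second, not asked at week 1, is "How many days last week did you take at least 2 of your study pills". The form is headed "Completed only at Week 1, 2, 3, 4, 8, and 12".

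The Prescription Form (Appendix C7) is written for 0.5 mg tablets. For weeks 2–12 it reads "take two tablets (1mg) twice daily, two tablets in the morning and two tablets in the evening". *Provision of varenicline* describes weekly supplies for four weeks and then four-weekly pick-ups, so the week-8 pick-up supplies weeks 9–12. Dose adjustments are permitted.

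In *Statistical Analysis for Study Objective 1*, one planned analysis will "assess factors associated with completion of varenicline regimen", using generalized estimating equations for binary repeated measures.

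**The concern.** The threshold and the question use different units, and the two sentences stand next to each other. No pill count is collected, so a rule in pills has no data to be scored on. If the rule is read in days instead, the requirement on each day is a single tablet, while the prescription form sets four from week 2.

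The time point adds a second problem. Week 8 is when the last supply is handed over, so the classification is settled before the last four weeks of treatment begin. Someone who stops the next day stays adherent.

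Two things are at stake. First, varenicline is the drug part of the intervention. If the reported adherence rate mixes people on the full prescription with people taking a fraction of it, it says little about exposure. Second, the completion analysis needs a definition of completion. The only adherence rule in the protocol cannot supply one, and sites that follow Table 3 would not collect the one adherence report that falls after week 8.

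**Working it through.** **Inputs.** Tablets per day come from Appendix C7: 1 on days 1–3, 2 on days 4–7, 4 in weeks 2–12, all 0.5 mg. The threshold (6 or 7, at week 8) comes from item 7 of the measures section. The treatment length of 12 weeks comes from Appendix C7 and *Provision of varenicline*.

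**Step 1: reproduce the prescription form's own figure.** Weeks 2–12: 2 tablets × 2 times a day × 0.5 mg = 2 mg a day, the total printed on the form. The form is internally consistent, so the tablet count can be relied on.

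**Step 2: tablets prescribed.**
- Week 1: 3 × 1 + 4 × 2 = 11
- Each of weeks 2–12: 4 × 7 = 28
- Whole course: 11 + 11 × 28 = 319

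**Step 3: the rule read literally, in pills.** Six or seven pills in week 8 is 6/28 = 21.4% or 7/28 = 25.0% of that week's tablets. A participant who took all 28 falls outside the range of six or seven.

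**Step 4: the rule read in days.** With at least one pill on each counted day, the guaranteed minimum is again 6–7 tablets.

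| Basis | Minimum tablets | Prescribed that week | Guaranteed share |
|---|---|---|---|
| At least 1 pill on 6–7 days, 0.5 mg tablets (Appendix C7) | 6–7 | 28 | 21–25% |
| At least 2 pills on 6–7 days (form's second item, not in the rule) | 12–14 | 28 | 43–50% |
| At least 1 pill on 6–7 days, if 1 mg tablets were dispensed (assumption: 2 a day) | 6–7 | 14 | 43–50% |

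The 1 mg row is an assumption because Appendix C1 lists both strengths but the prescription form uses only 0.5 mg. A permitted dose reduction would also raise the share for that participant.

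**Step 5: what the week-8 cut-off leaves out.** Weeks 9–12 are 4/12 = 33% of treatment weeks and 4 × 28 = 112 tablets. Two patterns that the rule, read in days, would class as adherent:
- Full dosing to the end of week 8, then none: (11 + 7 × 28)/319 = 207/319 = 64.9% of the course.
- One tablet a day to the end of week 8, then none: 56/319 = 17.6% of the course.

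**Step 6: the assessment weeks side by side.**

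| Source | 0 | 1 | 2 | 3 | 4 | 8 | 12 |
|---|---|---|---|---|---|---|---|
| Measures section, item 7 | X | X | X | | X | X | X |
| Adherence form | | X | X | X | X | X | X |
| Table 3 | | X | X | X | X | X | |

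The text lists week 0, when no pill has yet been taken, and omits week 3. Table 3 omits week 12.

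**The case against.** The strongest reply is that pills is a slip for days. The question comes directly before the definition, its answers run from 0 to 7, and six and seven are its top two values. That is the likely intention, and it disposes of the literal reading. It does not rescue the rule, because the floor in days is the same 6–7 tablets.

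A second reply is that 21–25% is a floor. Everyone who takes all four tablets every day also qualifies, and the protocol gives no figure for how many take only one. This stands: the amount of misclassification is unknown.

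Third, the form collects days with at least two pills, and it lists week 12. A stricter variable could therefore be derived later, and such detail is often left to a statistical analysis plan. This stands in part. But the protocol states a rule of its own, against four tablets a day the two-pill item still guarantees only half, and week-12 data will exist only if sites follow the form rather than Table 3. The measures section says the follow-up questionnaire also records length of varenicline use, but the Appendix B4 questions shown contain no such item.

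A reader might infer more than the documents support:
- **That the completion analysis will use the week-8 rule.** The protocol does not say so, and a single yes or no at week 8 is not a repeated measure. What can be said is that the rule could not serve, and that no other definition is stated.
- **That the trial's main conclusions are at risk.** Adherence is neither a primary nor a secondary outcome, the primary analysis is by intention to treat, and no adherence-adjusted analysis is planned.
- **That 28 tablets a week apply throughout the 12 weeks.** Week 1 has 11. The week-8 figures are unaffected.

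Finally, the protocol cites a source for its adherence measure that cannot be consulted here. The point is therefore not that counting days with at least one pill is an improper convention in general, but that it does not match this protocol's own prescription form and planned analysis.

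**Conclusion.** The point holds and should be corrected. As written, the rule cannot be scored. In its sensible reading it guarantees 21–25% of the tablets prescribed for week 8, on the assumption that the prescription form's 0.5 mg tablets are dispensed without dose reduction. The share is 43–50% if 1 mg tablets were dispensed. These are minimum shares, not estimates of what participants will take. The rule takes no account of the last third of treatment, so it cannot define completion of the regimen. The three assessment schedules contradict each other, and following Table 3 would lose the week-12 report for good. The damage is confined to a process measure and the completion analysis; the primary endpoint is untouched.

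**What to change.** 1. State the threshold in days: adherent means six or seven of the last seven days on which all pills prescribed for that day were taken. This wording works with either tablet strength and with permitted dose adjustments.
2. Reword the form's second item to ask for the number of days on which all pills prescribed for that day were taken.
3. Define completion of the regimen using the week-12 report as well as week 8. The week-12 item covers only the preceding week, so this improves the view of weeks 9–12 without making it complete.
4. Add the week-12 adherence mark to Table 3, and bring the list of weeks in the measures section into line with the form.

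The cost is one definition, one reworded item, one table mark and one corrected list. The reported adherence rate will be lower than under the present rule. Week 12 is already a study visit, but Table 3 assigns adherence to nurse prescribers and shows only research-assistant tasks there, so someone must be named to complete the form. No dose or clinical rule changes.
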